### Intervention periods and assessment time points

2.7

The intervention period will be 4 consecutive weeks, immediately following the conclusion of the training period. The 3 time points chosen for assessment interviews will be the following: 1 week before the start of the intervention, immediately after the 4 weeks of intervention, and 4 weeks after the end of the intervention period, to identify any remaining effects of PTNS.

### Assessment interviews

2.8

In all assessment time points, patients and/or their guardians will participate in semi-structured interviews to determine the functional results of the intervention, concerning patient bowel habits and quality of life. These interviews will be conducted by the same member of the research team and will last approximately 40 minutes. The following assessment instruments will be applied: a questionnaire addressing the current clinical status (Fig. 1); the modified Bristol Stool Form Scale for children (mBSFS-C)^[28–30]^ to analyze the stool consistency (see mBSTS-C, Supplemental Digital Content 4); the bowel function score (BF-S)^[31]^ to evaluate the functional status of bowel habits (see BF-S, Supplemental Digital Content 5); the fecal continence index (FCI) questionnaire,^[32,33]^ based on the clinical evaluation of fecal continence (see FCI, Supplemental Digital Content 6); the assessment of quality of life in children and adolescents with fecal incontinence (AQLCAFI)^[32,33]^ (see AQLCAFI, Supplemental Digital Content 7) and the pediatric quality of life inventory version 4.0 (PEDsQL 4.0)^[34,35]^ to assess the quality of life (see PEDsQL 4.0, Supplemental Digital Content 8); and a questionnaire addressing the evaluation of the applicability of the PTNS daily home sessions (Fig. 2).

**Figure 1 F1:**
[figure not shown]
Questionnaire addressing the current clinical status.

**Figure 2 F2:**
[figure not shown]
Questionnaire addressing the evaluation of the applicability of the PTNS daily home sessions. PTNS = posterior tibial nerve stimulation.

Additionally, each patient will be monitored throughout a standardized week diary (stool frequency, stool consistency according to the mBSFS-c, frequency of fecal incontinence episodes, painful defecation, abdominal pain, blood in stools, laxative use and their doses, and adverse effects such as pain, nausea, vomiting, diarrhea, and flatulence). This diary must be filled out for 7 days, initiating 7 days before each of the assessment time points. Patients who use laxative medication will have the dosage quantity monitored, and any alterations will be registered as possible outcomes in the conclusion of the study, both in the case of increase or reduction of dosage.

### Outcomes

2.9

Data analysis will be performed by focusing on the 3 assessment time points: assessment before the initiation of PTNS, immediately after the 4 weeks of intervention, and 4 weeks after the end of the intervention period. This analysis will be performed using the following clinical variables: number of defecations per week, number of episodes of fecal incontinence per week, need for diapers or underwear protection, need for medication for bowel habits, need for a special diet, straining and pain on defecation, presence of fecalomas, presence of abdominal pain, presence of bloody stools, need for enemas, and presence of perianal rashes or dermatitis. Also, we will analyze the results obtained by all the assessment instruments applied (mBSFS-C, BF-S, FCI questionnaire, AQLCAFI, and PEDsQL 4.0), to evaluate the outcomes of a functional status of bowel habits and the global quality of life.

As a secondary outcome, the applicability of PTNS will also be evaluated by the results of the specific questionnaire (Fig. 3), considering aspects that involve the practical difficulties for the application of this method and possible adverse events. All the situations that may be indirectly involved with the clinical results of PTNS, such as the increase or decrease of the laxative dose or any clinical or dietary changes, will also be analyzed as secondary endpoints.

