### Patient selection and recruitment

2.3

The estimated sample size is 28 patients, calculated for a paired *t* test (before and after intervention), based on an estimated mean increase of 7 defecations per month (according to data from previous PTNS studies^[25,26]^), an estimated standard deviation of changes = 12, a 2-tailed *α* = 0.05 and a test power *β* = 0.85. The sample will be comprised of children selected from the Pediatric Gastroenterology Outpatient and Pediatric Surgery Outpatient of the Clinics Hospital of the Botucatu Medical School -UNESP. The patients will be invited to attend an initial consultation to inform them about the study methods and apply the eligibility criteria.

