### Statistical analysis

2.10

Statistical and descriptive analysis will be performed to characterize the patients before the intervention. Then, a comparative statistical analysis will be carried out involving the results obtained for the variables analyzed in the 3 assessment time points. Continuous numerical data will be expressed as the mean ± standard deviation and median (interquartile range). Proportions will be presented as percentages with their respective reliability intervals. The comparison between the assessment time points will be made using different statistical tests, according to variables analyzed and the normality distribution of data obtained by Shapiro–Wilk and Kolmogorov–Smirnov tests. Nominal variables will be analyzed using the McNemar test. Continuous numerical variables of parametric distribution will be analyzed using the *t* test for paired samples and the analysis of variance. Continuous numerical variables of nonparametric distribution and ordinal variables will be analyzed using the Wilcoxon and Friedman tests. The significance level will be established at 5%, and the analysis will be performed using SPSS 22.0 software for Windows.

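### Sixteen efficacy outcomes at three time points share one 5% level and none is named primary, although the sample size rests on a single before/after contrast of defecation frequency

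*Protocol article*

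**What the plan says.** All references are to the protocol article.

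- **Outcomes (2.9).** The analysis covers three assessments: before stimulation, immediately after the 4 weeks, and 4 weeks later. The list begins "This analysis will be performed using the following clinical variables: number of defecations per week, number of episodes of fecal incontinence per week" and goes on to nine further clinical variables. The section then adds "we will analyze the results obtained by all the assessment instruments applied (mBSFS-C, BF-S, FCI questionnaire, AQLCAFI, and PEDsQL 4.0"), which makes five instruments.
- **Hierarchy (2.9).** The first use of a rank is "As a secondary outcome, the applicability of PTNS will also be evaluated by the results of the specific questionnaire". Changes in laxative dose and clinical or dietary changes are also called secondary. The visible text calls no outcome primary.
- **Statistical analysis (2.10).** "The significance level will be established at 5" percent, with no outcome or contrast singled out. The tests named are McNemar, paired t and Wilcoxon, each comparing two time points, and analysis of variance and Friedman, which can handle three.
- **Patient selection and recruitment (2.3).** The target is given as "The estimated sample size is 28 patients, calculated for a paired *t* test (before and after intervention"). The assumed effect follows, with the calculation described as "based on an estimated mean increase of 7 defecations per month". The assumed spread is "an estimated standard deviation of changes = 12", and the level and power are set by "a 2-tailed *α* = 0.05 and a test power *β* = 0.85".
- **Discussion (3).** The study is meant to demonstrate efficacy on bowel movements, stool consistency, retentive incontinence and quality of life together.

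**The concern.** The Outcomes section does set a hierarchy, but it ranks only the lower tier. Sixteen efficacy outcomes stand level with each other above it, each with two post-treatment visits. The 5% level and the planned power were worked out for one of these comparisons, and nothing in the text says that the efficacy conclusion rests on that one.

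The Discussion states a confirmatory aim. Without a designated test, the text leaves open which result would count as showing efficacy, so the error rate of that conclusion is not fixed in advance. The power figure also does not carry over to any of the other outcomes.

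**Working it through.** **1. Reproducing the plan's own figure.** Inputs from section 2.3: mean change 7, SD of changes 12, two-sided alpha 0.05, power 0.85.

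- Normal formula: n = ((1.960 + 1.036) × 12/7)² = 26.4, so 27.
- Exact noncentral t: power is 84.5% at n = 28 and 85.8% at n = 29.

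The stated 28 is reproduced within rounding. It serves one outcome, one contrast and one 5% test.

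**2. Counting the outcomes (section 2.9).** The clinical variables are defecations, incontinence episodes, diapers or protection, medication, special diet, straining and pain, fecalomas, abdominal pain, bloody stools, enemas, and perianal rash or dermatitis: 11. The instruments number 5. Total 11 + 5 = 16 (17 if straining and pain are counted separately).

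**3. Chance of at least one p<0.05 with no true change, independent tests.** The formula is 1 − 0.95^k.

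- k = 16 (one contrast per outcome): 1 − 0.95^16 = 56.0%
- k = 32 (both later visits against baseline): 80.6%
- k = 48 (all three pairs): 91.5%. This overstates somewhat, because the three pairs within an outcome are dependent; the simulation below allows for that.

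**4. Allowing for correlation and for McNemar tests.** This is a simulation of 28 patients, 16 outcomes and 3 time points with no true change. The correlations are assumptions, since the document gives none: within-patient correlation over time 0.5, between-outcome correlation as shown. In the mixed rows, 7 outcomes use a paired t test and 9 use an exact McNemar test.

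| Contrasts per outcome | Test mix | Corr. 0 | 0.3 | 0.5 | 0.7 |
|---|---|---|---|---|---|
| One | all continuous | 57% | 49% | 38% | 27% |
| One | mixed | 41% | 38% | 35% | 26% |
| Two | all continuous | 79% | 72% | 59% | 44% |
| Two | mixed | 65% | 59% | 53% | 43% |
| Three | all continuous | 89% | 82% | 70% | 53% |
| Three | mixed | 77% | 71% | 65% | 54% |

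**5. If the three-time-point test acts as a gate.** When pairwise tests are read only after a significant analysis of variance, the simulated error per continuous outcome is about 5.1%. For 16 independent outcomes this gives 1 − (1 − 0.051)^16 = 57%. Section 2.10 does not say whether the omnibus tests gate the pairwise ones.

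**6. The unit of the powered outcome.** Section 2.3 works per month and section 2.9 per week. Assume a 30-day month, that is 30/7 = 4.29 weeks. The weekly mean change is 7/4.29 = 1.63.

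- If the SD scales in proportion: 12/4.29 = 2.80. The ratio of mean to SD is unchanged at 7/12 = 0.58, and power at 28 stays 84.5%.
- If weekly counts vary independently (assumption): 12/√4.29 = 5.80. The ratio is 1.63/5.80 = 0.28, and power at 28 is about 30%.

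**The case against.** The strongest reply is that the lead outcome can be recognised without a label. Defecation frequency is the only variable powered, it comes first in the Outcomes list, and bowel movements come first among the aims in the Discussion. The abstract text, the supplementary checklist and the registry entry are not shown and might carry the label. This makes the repair easy, but it does not remove the defect: the Outcomes section assigns ranks itself and stops short of the one that matters. Section 2.3 also does not say which of the two later assessments is the after measurement.

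Four stronger readings are tempting, and the document does not support them.

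- A reader might infer that a chance positive result is more likely than not. That holds for 16 independent tests, or when all three pairs are tested ungated. With one contrast per outcome it falls below 50% at a correlation of about 0.3, or with exact McNemar tests. Several outcomes overlap in content (incontinence episodes, protection, the continence index and the incontinence quality-of-life tool), so correlation is to be expected.
- A reader might take 89% as the error rate of the plan. It treats every outcome as continuous and ignores both McNemar and the omnibus tests that section 2.10 names.
- A reader might fault the lack of a multiplicity adjustment. Such a method is commonly left to a statistical analysis plan, which may exist unseen. Section 2.10 also does not say that any single p<0.05 would count as success.
- A reader might conclude that stool frequency is collected twice, by interview and by diary. Only the diary is stated to record it; the interview questionnaire is in a figure that is not shown.

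**Conclusion.** The point stands in a limited form. Sixteen efficacy outcomes are left unranked, one 5% level covers them all, and only one before/after contrast of defecation frequency was powered. With no true change, the chance of at least one nominally significant result is about 56% for 16 independent tests. With one contrast each it is roughly 26% to 57% over the assumed correlations and test types, and it is up to about 89% for three ungated contrasts each. The exact figure depends on correlations that the document does not give, but the lowest value found is still about five times 5%.

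The stated 28 patients are adequate for a single primary test in the unit that was powered. Whether they are adequate for the weekly count in the Outcomes section depends on how the SD of 12 per month translates, with power between about 30% and 84.5% under the two assumptions shown.

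**What to change.** In the Outcomes section, name one primary test: change in defecation frequency from baseline to immediately after the 4 weeks of intervention, at two-sided 5%. Make the contrast 4 weeks after the end of the intervention and the other 15 outcomes secondary, reported as estimates with 95% confidence intervals and not as proof of efficacy.

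State the primary outcome and the sample-size assumption in the same unit, give the SD of change in that unit with its basis, and restate the power.

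The text change is about one paragraph and needs no extra visits. Naming the primary test does not by itself change the sample size. If the weekly count is kept and its SD does not scale in proportion, the restated power may show that 28 patients are too few. The other cost is that fewer secondary results can be called significant. Keeping all 16 outcomes co-equal would cost more: at a Bonferroni level of 0.05/16 = 0.0031, power for defecation frequency at 28 patients falls to about 45%, and about 52 patients would be needed for 85%.

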**Figure 3 F3:**
[figure not shown]
Flowchart of patients in the study.

To summarize the stages of the study, see the flow diagram in Figure 3 and the Supplemental Digital Content 9 (SDC-9) with standard protocol items: recommendations for interventionist tests.

### Statistical analysis

2.10

Statistical and descriptive analysis will be performed to characterize the patients before the intervention. Then, a comparative statistical analysis will be carried out involving the results obtained for the variables analyzed in the 3 assessment time points. Continuous numerical data will be expressed as the mean ± standard deviation and median (interquartile range). Proportions will be presented as percentages with their respective reliability intervals. The comparison between the assessment time points will be made using different statistical tests, according to variables analyzed and the normality distribution of data obtained by Shapiro–Wilk and Kolmogorov–Smirnov tests. Nominal variables will be analyzed using the McNemar test. Continuous numerical variables of parametric distribution will be analyzed using the *t* test for paired samples and the analysis of variance. Continuous numerical variables of nonparametric distribution and ordinal variables will be analyzed using the Wilcoxon and Friedman tests. The significance level will be established at 5%, and the analysis will be performed using SPSS 22.0 software for Windows.

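### Two normality pre-tests with no rule for disagreement choose the test, even for the outcome sized on a paired t test, and nominal outcomes have no test across the three visits

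*Protocol article*

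**What the plan says.** Section 2.9 sets the frame: "Data analysis will be performed by focusing on the 3 assessment time points", namely before stimulation, at the end of the four weeks, and four weeks later. Section 2.10 repeats it: "a comparative statistical analysis will be carried out involving the results obtained for the variables analyzed in the 3 assessment time points".

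Section 2.10 then gives a general rule: "The comparison between the assessment time points will be made using different statistical tests, according to variables analyzed and the normality distribution of data". Under it, tests are assigned by type of variable:

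- Nominal: "Nominal variables will be analyzed using the McNemar test". Nothing else is named for them.
- Continuous and judged normal: these "will be analyzed using the *t* test for paired samples and the analysis of variance".
- Continuous and judged non-normal, and ordinal: "Continuous numerical variables of nonparametric distribution and ordinal variables will be analyzed using the Wilcoxon and Friedman tests".

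For a continuous variable, the choice between the last two sets is made "according to variables analyzed and the normality distribution of data obtained by Shapiro–Wilk and Kolmogorov–Smirnov tests". The only level given is 5%, and section 2.10 names neither the pairs of visits to be tested nor any adjustment.

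Section 2.3 derives the 28 patients from a paired t test, before against after, for a mean increase of 7 defecations per month with a standard deviation of changes of 12.

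**The concern.** There are two separate problems, and both lie in rules the article states.

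**The test for the sized outcome is left open.** Section 2.3 commits to a test of the mean change in defecations. Section 2.10 makes the test for the same variable depend on the observed data. If normality is rejected, the paired t test gives way to Wilcoxon, which tests for a symmetric shift about zero and not for a mean change. The hypothesis and the estimate are then settled after the data are seen, and the stated power applies only if the data stay on the t-test branch. Two normality tests are named without saying which one decides, so conflicting results leave the choice to the analyst. Section 2.8 takes stool frequency from a seven-day diary, so this is a small count for which non-normality is a realistic result.

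**Nominal outcomes have no overall test.** The other variables get a two-visit test and a multi-visit test. The yes/no items of section 2.9 (fecalomas, abdominal pain, bloody stools, enemas, perianal rash and others) get only the two-visit test. An analyst who follows the text can compare three visits only by running several McNemar tests, each at 5%.

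**Working it through.** **1. The plan's own figure.** Inputs from section 2.3: change 7, SD of changes 12, two-sided alpha 0.05, power 0.85 (printed there as beta).

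- Normal approximation: n = ((1.960 + 1.036) × 12 / 7)² = 26.4, so 27.
- Exact noncentral t at n = 28: df = 27, noncentrality = (7/12) × √28 = 3.09, power 0.845. At n = 29 the power is 0.858.

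The 28 patients are reproduced to within rounding, for a paired t test on one before–after contrast.

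**2. The pre-test step.** Simulation at n = 28 with 4,000 trials per distribution. Changes have mean zero, Shapiro–Wilk at 5% decides, and the paired t test is used if normality is not rejected, otherwise Wilcoxon. The distributions are assumptions, because the article gives none.

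| Distribution of changes | Two-stage rule | Paired t alone | Wilcoxon alone | The two normality tests disagree |
|---|---|---|---|---|
| Normal | 0.058 | 0.055 | 0.053 | 5% |
| t with 3 df | 0.045 | 0.038 | 0.042 | 39% |
| Laplace | 0.048 | 0.045 | 0.047 | 33% |
| Centred exponential (strong skew) | 0.153 | 0.075 | 0.152 | 86% |

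A separate simulation of mean-zero skewed changes gave 16% for the two-stage rule and 7% for the paired t test. In the skewed case the two-stage result nearly equals Wilcoxon alone, because almost every trial is sent there. Wilcoxon is not malfunctioning: it rejects a symmetric distribution about zero, which is false here although the mean is zero.

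The disagreement column uses Kolmogorov–Smirnov without the Lilliefors correction. With the correction, and differences of skewed weekly counts (gamma–Poisson, means 2 and 3.75, also assumed), Shapiro–Wilk rejected in 53% of trials, Kolmogorov–Smirnov in 66%, and the two disagreed in about 25%. So the rate depends on the distribution and on the form of the test, but only the normal case made it small.

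**3. Nominal outcomes.** Reference: three independent tests at 5% give 1 − 0.95³ = 0.143. The tests share visits, so the real figure is lower. Simulation at n = 28 with 20,000 trials, no change over time, prevalence 0.5, and a child effect with latent correlation 0 to 0.7 (assumed):

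| Procedure for one item | Chance of at least one false positive |
|---|---|
| Three McNemar tests, uncorrected chi-square | 0.109–0.115 |
| Three McNemar tests, exact | 0.044–0.069 |
| One Cochran's Q test | 0.048–0.051 |

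Adding prevalence 0.7 gave 0.103–0.115 for the chi-square form and 0.054–0.070 for the exact form. Rounded over all runs, that is about 10–12% and 4–7%. Cochran's Q followed by exact McNemar gave 4.1–4.7%.

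**The case against.** **The tests suit the design.** A reader might infer that the tests in general do not fit three repeated assessments. The article does not support that. Friedman is a test for three or more related measurements, and paired t, Wilcoxon and McNemar are each valid for a given pair of visits. The gap across three visits concerns nominal variables only.

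**The ANOVA is probably within-child.** A reader might also infer that the unqualified analysis of variance treats a child's visits as independent, and that power falls to 0.57 or 0.38. The text does not show this. The phrase stands next to a paired t test and parallel to Wilcoxon and Friedman, so a repeated-measures analysis is the natural reading. The 0.57 and 0.38 belong to an unpaired two-sample t test with 54 df, which the article does not plan. The planned paired contrast has power 0.845.

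**The McNemar inflation depends on the form.** This is right. Over three pairs, one simulation put the exact and the continuity-corrected forms at about 3–7%. Section 2.7 gives the purpose of the last visit as finding remaining effects, which suggests two contrasts with baseline. With two, the exact form gave 0.024–0.049. But the article fixes neither the form nor the pairs, so the higher figure is not excluded.

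**The pre-test harm rests on invented distributions.** This is partly right. With normal or symmetric changes the two-stage error stays near 5%, and the 15–16% needs strong skew with Shapiro–Wilk deciding. If the uncorrected Kolmogorov–Smirnov test decided, the result would lie nearer to the t test. That sensitivity is itself the consequence of having no rule. The mismatch with section 2.3 does not depend on any simulation.

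**Missing visits and other detail belong in a fuller plan.** Accepted. Handling of incomplete cases is not part of this point.

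**Conclusion.** The point holds in two parts.

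First, the test for defecations is fixed in section 2.3 and left to the data in section 2.10, through two normality tests with no rule for disagreement. The cost ranges from almost nothing (0.058 against 0.055 with normal changes) to about a doubling of rejections under a zero mean change (about 15–16% against 7%) with strong skew. The article does not give the distribution of changes, so this is a range and not an estimate.

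Second, nominal outcomes have no test across the three visits. If all three pairs are tested unadjusted, the error per item is about 10–12% with the uncorrected chi-square form. With the exact form it is about 4–7%, which is little or no inflation.

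The sample size is not affected, and the paired power of 0.845 stands as long as the paired t test is the analysis. This is worth correcting because it is cheap and the article places the study in recruitment. It does not invalidate the design.

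**What to change.** Reword section 2.10:

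1. Remove the normality tests as the rule for selecting a test.
2. For defecations, fix the paired before–after mean change with its 95% CI and paired t test, matching section 2.3. Report Wilcoxon signed-rank as a sensitivity analysis that does not replace it. The paired t test is not perfect under strong skew (about 7%), which is a reason to show both.
3. For the other continuous outcomes, use a within-child analysis over the three visits, either repeated-measures ANOVA named as such or a mixed model that uses all available visits. Keep Friedman and Wilcoxon for ordinal scores.
4. For binary outcomes, use Cochran's Q over the three visits first, then exact McNemar for the pairs only if Q is significant. With three visits this order also protects the pairwise tests: if one visit differs from the other two, only one true null hypothesis is left to reject wrongly.

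The cost is a few sentences and slightly more analysis work. The number of patients and the visits do not change.
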